#### Efficacy evaluation secondary outcomes

An overview of the planned analyses is provided in Table 2. Time to improvement during the IVIg restabilization period will be analyzed separately for INCAT total score (decrease by ≥ 1 point), mean grip strength (increase by ≥ 8 kPa), dominant/nondominant), and I-RODS (increase by ≥ 4 points), as well as overall using Kaplan-Meier estimates. For the overall analysis, if a subject has multiple dates of improvement, the first will be used. Subjects who do not record an improvement will be censored at the date of their last visit. Analyses will be based on the PSDS. Time to improvement after relapse in the SC treatment period will be analyzed on the INCAT total score using the RSDS. An overview of all other planned secondary analyses is provided in Table 2.

**Table 2 Tab2:** Analyses performed at each study period for secondary outcomes, IgG levels, and health-related quality of life variables

	Period (analysis set)		
	IVIg restabilization (PSDS)	SC treatment (ITTS, PPS)	IVIg rescue (RSDS)
INCAT			
Total	Overall: - Descriptive statistics - Change from reference visit - Time to first improvement on IgPro10: Kaplan-Meier estimates	- By treatment and by treatment and subgroup: - Descriptive statistics - Comparison between treatments of changes from reference visit: exact Jonckheere-Terpstra test^a^ - Comparisons between each IgPro20 dose group and placebo group, and the comparison between the two IgPro20 dose groups of changes from reference visit: Wilcoxon rank sum test^b^ - Time to CIDP relapse or withdrawal for any other reason: Kaplan-Meier estimates^c^	Overall: - Descriptive statistics - Change from reference visit - Time to improvement after CIDP relapse with IgPro10 rescue: Kaplan-Meier estimates
Mean grip strength (Dominant/non-dominant hand), MRC sum score, I-RODS			
	Overall: - Descriptive statistics - Change from reference visit - Time to first improvement on IgPro10: Kaplan-Meier estimates	By treatment and by treatment and subgroup: - Descriptive statistics - Comparison between treatments of changes from reference visit; exact Jonckheere-Terpstra test^a^ - Comparisons between each IgPro20 dose group and placebo group, and the comparison between the two IgPro20 dose groups of changes from reference visit; Wilcoxon rank sum test^b^	Overall: - Descriptive statistics - Change from reference visit
Electrophysiological parameters (average distal latency, average proximal latency, overall average conduction velocity, average conduction block, and average compound muscle action potential amplitude)			
		By treatment and by treatment and subgroup: - Descriptive statistics - Change from reference visit - Between-treatment comparisons of the changes from baseline: analysis of variance (ANOVA) model^d^	
IgG level			
	Overall: - Descriptive statistics - Change from reference visit	By treatment and by treatment and subgroup: - Descriptive statistics - Change from reference visit	Overall: - Descriptive statistics - Change from reference visit
EQ-5D dimensions, TSQM, WPAI-GH			
	Overall: - Descriptive statistics	By treatment: - Descriptive statistics - Change from reference visit - Comparison between treatments of changes from reference visit; exact Jonckheere-Terpstra test^a^ - Comparisons between each IgPro20 dose group and placebo group, and the comparison between the two IgPro20 dose groups of changes from reference visit; Wilcoxon rank sum test^b^	Overall: - Descriptive statistics
Patient preference for treatment questionnaire			
		By treatment: - Descriptive statistics	

*EQ-5D* EuroQoL 5-Dimension Questionnaire, *IgG* immunoglobulin G, *ITTS* intention-to-treat set, *IVIg* intravenous immunoglobulin, *MRC* Medical Research Council, *PSDS* pre-randomization safety data set, I-*RODS* Inflammatory-Rasch-built Overall Disability Scale, RSDS, rescue safety data set, *SC* subcutaneous, *TSQM* Treatment Satisfaction Questionnaire for Medication, *WPAI-GH* Work Productivity and Activity Impairment Questionnaire for General Health

^a^Exact Jonckheere-Terpstra test see ref [54]

^b^For each pair-wise comparison, the one-sided *p* value from the Wilcoxon rank sum test and the Hodges-Lehmann estimate of the median difference between treatments will be presented together with the corresponding two-sided 95 % Moses confidence interval

^c^Overall between-treatment comparison will be performed using the log-rank test for trend, all pair-wise comparisons will be performed using the log-rank test

^d^Treatment and region (Japan, non-Japan) will be used as explanatory variables. Within the framework of this ANOVA model, comparisons of each IgPro20 dose with placebo, and the comparison of the two IgPro20 doses will be performed. For these comparisons, the least squares mean for each treatment group, an estimate of the difference between treatments (if applicable), corresponding 95 % confidence interval and 2-sided p-values will be presented

**Table 3 Tab3:** Overview of sensitivity analyses

Withdrawal reasons	Assignment of patients in:				
	Primary analysis	Sensitivity analysis			
		A	B	C	D^a^
The patient experiences a CIDP relapse during the SC treatment period (lack of efficacy)	Relapser	Relapser	Relapser	Relapser	Relapser
The investigator advises that the patient’s safety or wellbeing could be compromised by further participation in the study (physician decision)	Relapser	Non-relapsers	Relapser	Not used for analysis	Censored
The patient receives prohibited medication (protocol violation)					Censored
Other withdrawal reason (other, adverse event, death, lost to follow-up, protocol violation, study termination by sponsor, and withdrawal by patient)			Non-relapsers		Censored
Patient continues to study end	Non-relapsers	Non-relapsers	Non-relapsers	Non-relapsers	Non-relapsers

*CIPD* chronic inflammatory demyelinating polyneuropathy, *SC* subcutaneous

^a^Exploratory sensitivity analysis

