#### Sensitivity analyses

Sensitivity analyses will be performed with modified primary endpoint definitions to investigate the potential bias due to the inclusion of dropouts without CIDP relapse (patients who withdraw from the study due to any reason other than CIDP relapse) in the primary endpoint. For each sensitivity analysis, the analysis performed for the primary endpoint will be repeated, including the exact Cochran-Armitage trend test, one-sided Fisher’s exact tests for the pair-wise treatment comparisons and all estimates and confidence intervals.

For the primary analysis, only patients who complete the study without recording a relapse are considered nonrelapsers. All other patients, including those who withdraw for any reason other than relapse, are considered relapsers. Four sensitivity analyses will be performed that assign a different status’ (relapse or nonrelapser) to patients who are withdrawn from the study for reasons other than efficacy (Table 3):

**Table 4 Tab4:** Subgroup analyses by endpoint

Subgroup	Primary efficacy analysis of Relapse rate	INCAT total score	Mean grip strength (dominant/ nondominant hand)	I-RODS	MRC sum score	Time to relapse or withdrawal for any other reason	IgG serum levels
Sex (male/female)	X	X	X	X	X	X	
Age group (≥18 years to ≤ 65 years, and > 65 years)	X	X	X	X	X	X	
Prestudy IVIg treatment modality (IVIg maintenance therapy, acute IVIg therapy)^a^	X	X	X	X	X	X	
Region (Japan/non-Japan)	X						X
Relapse status (yes/no)							X
IVIg Dependency criterion: I-RODS or grip strength	X^b^						

*IgG* immunoglobulin G, *INCAT* Inflammatory Neuropathy Cause and Treatment, *IVIg* intravenous immunoglobulin, *MRC* Medical Research Council, *I-RODS* Inflammatory-Rasch-built Overall Disability Scale

^a^For Japanese subjects only

^b^This subgroup analysis will only be conducted if the group size is ≥ 30

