#### Examination of subgroups

Exploratory subgroup analyses will be performed for endpoints in the SC treatment period (Table 4). The subgroup analysis for age group will only be conducted if the size of the smallest group exceeds 10 patients. The percentage of patients experiencing a CIDP relapse (or withdrawing for any other reason) during the SC treatment period within each subgroup category will be presented by treatment group.

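### Table 2 plans significance tests inside each subgroup category, and the article states no comparison of the treatment effect between categories

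*Protocol article*

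**What the plan says.** In the Protocol article, Table 2 (Efficacy evaluation secondary outcomes, SC treatment column) puts the INCAT analyses under a single lead-in: "By treatment and by treatment and subgroup: - Descriptive statistics - Comparison between treatments of changes from reference visit: exact Jonckheere-Terpstra test". The next entry under that lead-in, a rank-sum test for each pair of arms, reads "Comparisons between each IgPro20 dose group and placebo group, and the comparison between the two IgPro20 dose groups of changes from reference visit: Wilcoxon rank". The same row adds time to relapse or withdrawal; footnote c assigns it a log-rank trend test and log-rank tests for every pair of arms. The row for grip strength (each hand), MRC sum score and I-RODS carries the same lead-in and the same trend and pairwise tests.

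Footnote b says what accompanies each pairwise test: "the one-sided *p* value from the Wilcoxon rank sum test and the Hodges-Lehmann estimate of the median difference between treatments will be presented", with a two-sided 95% Moses interval.

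Table 4 marks INCAT, grip strength, I-RODS, MRC and time to relapse or withdrawal for three factors: sex, "Age group (≥18 years to ≤ 65 years, and > 65 years"), and prestudy IVIg modality, the last for Japanese subjects only. Examination of subgroups sets the status: "Exploratory subgroup analyses will be performed for endpoints in the SC treatment period (Table 4"). For the primary endpoint it says only that the percentage with an event "within each subgroup category will be presented by treatment group"; no test is named there.

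No section or table of the article states a treatment-by-subgroup term or any other comparison of effects between categories.

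**The concern.** The question a subgroup analysis should answer is whether the treatment effect differs between, say, men and women. A p-value computed within men and another within women do not answer it. Each depends on the effect and on the number of patients in that category, so a split verdict can arise from category size and chance alone.

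This is more than a method left open for the analysis plan. The article names the tests to be run inside the categories. The row for EQ-5D, TSQM and WPAI-GH is headed by treatment only, so the subgroup wording in the other rows looks deliberate. The endpoints are also handled unevenly: the primary endpoint gets percentages per category, while the secondary endpoints get a full set of tests. At stake is the reading of exploratory results. The confirmatory analysis is not affected.

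**Working it through.** **1. Count of planned tests.** Factors: sex, age, Japan-only modality (Table 4), 2 categories each. Endpoints: INCAT, grip strength dominant, grip strength non-dominant, MRC, I-RODS, time to relapse or withdrawal. Tests per endpoint: 1 trend + 3 pairwise. 3 × 2 × 6 × 4 = 144 on the ITTS. Table 2 heads the column with ITTS and PPS, so 288 over both.

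**2. Reproducing the plan's own figure.** Inputs from Sample size: event rates 35% (high dose), 52% (low dose), 65% (placebo); one-sided 2.5%; power 90%; 58 per arm. For scores −1, 0, 1 the mean rate is 0.5067, and

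n = [(1.960·√(2·0.5067·0.4933) + 1.282·√(0.35·0.65 + 0.65·0.35)) / (0.65 − 0.35)]² = [(1.386 + 0.864)/0.30]² ≈ 56.3, so 57.

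Full enumeration of the exact Cochran-Armitage test first reaches 90% at 57 per arm (90.15%). At 58 it gives 87.9%, because discreteness lowers the attained size to 0.0175; the asymptotic and mid-p versions give 90.9%. The stated 58 is reproduced to within one or two patients per arm.

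**3. Discordance with identical true effects.** The two categories contain different patients, so their tests are independent. With within-category powers a and b,

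P(exactly one significant) = a(1 − b) + b(1 − a).

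The yardstick is the exact trend test at the design rates. Assumptions: one-sided 0.025 within each category (the article sets no level for subgroups), the splits shown, and equal arm sizes within a category.

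| Split of the 58 per arm | Power, larger | Power, smaller | Exactly one significant |
|---|---|---|---|
| 29/29 | 63.4% | 63.4% | 46.4% |
| 35/23 | 69.5% | 44.3% | 52.2% |
| 39/19 | 70.5% | 39.9% | 54.1% |
| 46/12 | 82.7% | 21.4% | 68.7% |

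Example, 39/19: 0.705 × 0.601 + 0.399 × 0.295 = 0.4237 + 0.1177 = 0.541.

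**4. Check with the test Table 2 names.** The Jonckheere-Terpstra test was simulated (4,000 runs, normal outcome, linear dose effect tuned to about 90% overall power). Discordance was 48% (29/29), 54% (39/19) and 63% (46/12). A two-sided 5% test comparing the dose slopes between categories rejected in 4.3–5.7% of runs over all scenarios simulated, including no effect and about 55% overall power.

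**5. Dependence on overall power** (normal approximation):

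| Overall power | Even split | 2:1 split |
|---|---|---|
| No effect | 4.9% | 4.9% |
| 50% | 41% | 42% |
| 80% | 50% | 54% |
| 90% | 47% | 52% |
| 99% | 24% | 33% |
| 99.9% | 10% | 18% |

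**6. Pairwise contrasts.** Fisher tests at the design rates, 29/29: placebo vs high dose has power 52.8% per category, so 2 × 0.528 × 0.472 = 50%; low vs high dose 17.2%, so 28%; placebo vs low dose 10.5%, so 19%.

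**The case against.** The case against is substantial, and several parts of it stand.

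- *The article condenses a fuller plan.* An interaction contrast may sit in the analysis plan, which is not shown. This stands as a limit: a reader might infer that no between-category comparison will be made, and the article cannot support that. It does support that within-category tests are fixed in Table 2; an added interaction test would not remove them.
- *The analyses are exploratory.* True. A reader might infer that the trial intends to claim effect modification whenever one category is significant and the other is not. No passage plans that inference or attaches a decision rule to subgroups.
- *P-values are not the only output.* A reader might infer that they are. Footnote b contradicts this for the pairwise comparisons of INCAT, grip strength, MRC and I-RODS, where Hodges-Lehmann estimates and intervals are planned. No such estimate is stated for the trend or log-rank tests.
- *A misleading split about half the time.* As an unconditional statement this is unsupported. The yardstick borrows the primary endpoint's test and rates, and the article gives no power for any secondary outcome and no subgroup sizes.
- *The subgroup lead-in is loose.* Table 2 also uses it for electrophysiology, which has no column in Table 4. The endpoints at issue here, however, are marked in both tables.
- *Minimum sizes.* One rule is "The subgroup analysis for age group will only be conducted if the size of the smallest group exceeds 10 patients"; the other, for the dependency criterion, is "This subgroup analysis will only be conducted if the group size is ≥ 30". A reader might infer an error that calls for a common minimum. They are rules for different factors, so they do not conflict. Eleven patients, about 4/4/3 per arm, is a floor and not an expected size. A 4 vs 3 Wilcoxon test cannot go below 1/35 = 0.029, but 4 vs 4 can reach 1/70 = 0.014 and the exact trend test 1/11,550.

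**Conclusion.** The point holds in a limited form. The stated within-category tests cannot show whether the treatment effect differs between categories, and the article states no analysis that does. If an endpoint has overall power near 90% and categories split between even and about 2:1, identical effects produce a significant trend in exactly one category in about 46–54% of trials. A direct interaction test would be wrong in about 5%. The power, the splits and the 0.025 level within categories are all assumptions. Outside them the figure moves widely: about 5% with no effect, 19–28% for placebo vs low dose and low vs high dose, 24% or less for an even split once overall power reaches 99%, and 69% for a 46/12 split. This is a worthwhile, low-cost improvement to exploratory reporting and no threat to the primary conclusion.

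**What to change.** In Table 2, for the SC treatment period:

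1. Drop the within-category Jonckheere-Terpstra, Wilcoxon and log-rank p-values.
2. Keep the Hodges-Lehmann estimates and 95% intervals per category that footnote b already provides for pairwise comparisons.
3. Add an effect estimate with 95% interval per category for time to relapse or withdrawal. In Examination of subgroups, add the difference in proportions with interval for the primary endpoint.
4. Add one treatment-by-subgroup contrast per factor and endpoint, for example dose score × subgroup in an ordinal, logistic or Cox model.
5. State that these contrasts have low power and that a non-significant interaction does not prove equal effects.

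The cost is wording in the tables and analysis plan plus a few model fits. The drawback is the low power. With an even split, the between-category difference has twice the standard error of the overall effect. If the overall effect has 90% power (1.960 + 1.282 = 3.242 standard errors), an interaction as large as that effect lies 3.242/2 = 1.621 standard errors from zero. Its power at two-sided 5% is about P(Z > 1.960 − 1.621) = P(Z > 0.339) ≈ 37%.

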### Randomization and masking

Randomization will be controlled centrally based on a predefined randomization schedule using block randomization using an Interactive Web and Voice Response System (IWRS) system maintained by an external service provider. Randomization was stratified by for regions (Japan/non-Japan). Access to the randomization list is restricted to designated people of the service provider not involved in the conduct or analysis of the trial. The treating physician (see below) transmits data critical for the randomization procedure via the IWRS system. All patients and study personnel will be blinded. Standard measures will be taken for the placebo and IgPro20 to ensure adequate blinding. A “two-physician” approach is implemented to reduce the chance of potential study unblinding. The “treating” physician will be the primary contact for the patient and will be responsible for all patient-related questions, adverse event (AE) evaluation, and for all other study-related tasks. A second “evaluating” physician will be responsible for assessment of efficacy variables. The evaluating physician does not have access to any data collected by the treating physician. For interim analysis and ongoing risk-benefit evaluations, members of the independent data monitoring committee may need to be unblinded. Access to study documents containing information on IgG levels and treatment groups will be restricted to people not directly involved in the study.

In case of an emergency and if necessary to make an adequate treatment decision, the blind can be broken by the treating physician using the interactive voice/web response system. Patients in whom the blind code has been broken will be discontinued from the study after a completion visit.

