### Statistical analysis

#### Sample size

The study is powered to show that the percentage of patients having a CIDP relapse or withdrawing from the study during the SC treatment will be statistically significantly higher for the placebo group than for at least one of the examined IgPro20 doses arms. A monotonic dose response is expected with placebo ≥ IgPro20 low dose ≥ IgPro20 high dose.

The percentages of patients who reach an endpoint (i.e., relapse or withdraw during SC treatment) will be assumed to be 35 % for the IgPro20 high dose, 52 % for the IgPro20 low dose, and 65 % for placebo. These numbers are based on the (recalculated) data of the ICE study extension period [32], which are adopted based on differences in the study setup. The fraction of IVIg independent patients included is assumed to be 15 %; those patients are believed to have a relapse rate of 10 % regardless of treatment.

The exact Cochran-Armitage trend test with equally spaced scores has been used for the sample-size calculation. With a one-sided significance level of 2.5 %, a sample size of 58 is needed in each treatment arm to achieve a power of 90 % in an intention-to-treat analysis based on the above assumptions. Thus, the overall sample size will be 174 patients treated either with IgPro20 or placebo. Accounting for patients who will not pass the IgG dependency test and IVIg restabilization period, up to 350 patients need to be screened to ensure that 174 patients are treated with IgPro20 or placebo.

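### The secondary rank tests of change are valid, but they use neither the randomisation stratum (region) nor baseline adjustment beyond subtraction: a cheap, optional gain in efficiency

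*Protocol article*

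**What the plan says.** All references are to the protocol article.

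- **Randomization and masking:** "Randomization was stratified by for regions (Japan/non-Japan").
- **Assessment schedule of primary and secondary outcome variables:** INCAT, grip strength, MRC sum score and I-RODS are all measured at baseline (week 10 or 13) and at the completion visit.
- **Efficacy evaluation secondary outcomes, Table 2, SC treatment column:** for these four outcomes, "Comparison between treatments of changes from reference visit: exact Jonckheere-Terpstra test". Pairwise comparisons use the Wilcoxon rank sum test. Footnote b adds the one-sided p value, the Hodges-Lehmann estimate and the Moses interval. Neither a stratum nor a baseline covariate is named.
- **Table 2, footnote d**, for the electrophysiological parameters, which the article lists as exploratory: "Treatment and region (Japan, non-Japan) will be used as explanatory variables". That model has no baseline term.
- **Table 4:** region is a subgroup only for the primary endpoint and for IgG levels, so it does not enter the analysis of the four secondary scores there either.
- **Sample size:** the 58 per arm is derived for the primary endpoint alone. No power is stated for the secondary tests.

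**The concern.** A factor that stratified the randomisation would normally appear in the analysis. Here it appears in the model for an exploratory outcome and not in the tests of the secondary outcomes, and no reason is given.

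Subtracting baseline is also not the same as adjusting for it. When the baseline score contains noise, the change score is negatively correlated with it, and that part of the variation stays in the treatment comparison. The trial is not sized for these outcomes, so their power depends on the analysis chosen. What is at stake is some avoidable loss of power, not bias and not a false-positive risk.

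The article names the tests, the estimator, the interval and, where used, the explanatory variables. This is therefore a stated choice, not a detail left to an unseen analysis plan.

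**Working it through.** **1. The plan's own figure.** The Sample size section assumes endpoint rates of "35 % for the IgPro20 high dose, 52 % for the IgPro20 low dose, and 65 % for placebo". It sizes the primary endpoint with an exact Cochran-Armitage test using equal score spacing, one-sided alpha 0.025, target power 90 % and 58 per arm. By full enumeration of the exact test, the smallest n per arm reaching 90 % is 57 (power 0.9015). The asymptotic test also gives 57 (0.904). The stated 58 reproduces to within one patient. At exactly 58 the asymptotic power is 0.909 and the exact power is 0.879, a sawtooth dip. None of this depends on the secondary tests; it only fixes 58 per arm as the size available to them.

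**2. Baseline adjustment, normal-shift model.** The correlation r between baseline and completion score is not in the documents, so a range is assumed. Adjustment multiplies the variance of the comparison by 1 − corr(change, baseline)². With equal variances at both visits this is (1 − r²) / [2(1 − r)] = (1 + r)/2. The equivalent size is 58 divided by that ratio. Starting from 80 % power, the new power is Φ(2.80/√ratio − 1.96).

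| r | ratio | 58 per arm is worth | 80 % becomes |
|---|---|---|---|
| 0.5 | 0.75 | 77 | 90 % |
| 0.7 | 0.85 | 68 | 86 % |
| 0.8 | 0.90 | 64 | 84 % |
| 0.9 | 0.95 | 61 | 82 % |

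**3. Simulation of the planned trend test.** Three arms of 58, 2,000 runs per setting, large-sample Jonckheere-Terpstra test, one-sided 0.025, assumed 7 % Japanese share, no regional effect. The adjusted version ranks the change, regresses it on baseline and tests the residuals.

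| r | raw change | baseline-adjusted |
|---|---|---|
| 0.5 | 80.7 % | 88.5 % |
| 0.7 | 78.6 % | 83.6 % |
| 0.9 | 77.8 % | 79.4 % |

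**4. Region alone** (van Elteren weights, same simulation).
- No regional effect: about 0 points.
- 7 % share, 0.5 SD effect on change: 0 to 2 points.
- 20 % share, 0.5 SD effect: about 1 to 6 points; for example, 74.0 % to 79.5 % at r = 0.9.

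The shares and effects are assumptions.

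**5. A model closer to this design.** Patients are randomised only after a stable INCAT score at two visits, and 35 to 65 % are then expected to relapse or withdraw. Change may thus be near zero for most patients, with a drop in relapsers.

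Take unit baseline variance, reliability 0.85, and a drop of 1 SD in 65 % (or 35 %) of an arm, independent of baseline:
- Cov(change, baseline) = −(1 − 0.85) = −0.15.
- Var(change) = 2 × 0.15 + 0.65 × 0.35 × 1² = 0.5275.
- Ratio = 1 − 0.15²/0.5275 = 0.957, that is, 4 % less variance.
- Here r = 0.85/√1.2275 = 0.77, for which (1 + r)/2 would promise 12 % less.

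So r alone does not fix the gain. One set of mixture simulations (58 per arm, 65 % against 35 % relapsing, reliability 0.85 to 0.99, drops of 0.4 to 1 SD, 6,000 runs per setting) changed power by −0.6 to +1.2 points. A second set gave −0.2 to +4.

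**6. Validity.** With no treatment effect (4,000 runs, r = 0.7, 10 % share, 0.5 SD regional effect), rejection rates were 2.2 % for raw change, 2.4 % region-stratified, 2.2 % baseline-adjusted and 2.4 % with both. The Monte Carlo error is about √(0.025 × 0.975/4000) = 0.25 points, so these do not differ from 2.5 % in any way that matters.

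**The case against.** The strongest reply is that nothing here is wrong. The tests are prespecified, valid and suited to ordinal scores. The Wilcoxon p value comes with a matching Hodges-Lehmann estimate and Moses interval in score units. Rank analysis of covariance has no such matching interval, so test and interval could occasionally disagree. The trend test is planned as exact, and a stratified replacement needs its own exact form. All of this stands, and it rules out calling the change free.

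The size of the gain is also open to challenge. The only related figure in the article, the I-RODS repeat-measurement intraclass correlation of 0.97 to 0.99 (Appropriateness of measurements), points to the small-gain end. It is not a 24-week correlation, so it limits the measurement-error part without settling r. The mixture model points the same way.

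A careless adjustment can lose power. In simulation, summing strata without weights lost up to about 4 points, and residualising the ranked final score on baseline lost about 3 to 5 points at r = 0.9.

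A reader might infer that the secondary outcomes ignore baseline altogether, or get a weaker analysis than the exploratory ones. The documents do not support either. Change subtracts baseline, and the nerve-conduction model adds only region, the part worth least, with no baseline term of its own.

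What survives is narrower: the stratification factor is used in one place and omitted in another without a reason, and a collected baseline is not used for adjustment.

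**Conclusion.** The point holds as an efficiency improvement for secondary outcomes. Table 2 leaves its between-treatment tests unstratified by region and adjusts for baseline only by subtraction, although footnote d uses region.

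Which end of the range in the working applies depends on the baseline-to-completion correlation, the Japanese share, any regional effect and how relapse shapes the change scores. The documents give none of these. Under every model tried, a well-chosen adjustment cost essentially no power (at worst −0.6 points).

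One might conclude that the trial forgoes some 10 points of power on its secondary outcomes. That figure belongs to r = 0.5 under the most favourable model and is not a property of this design. Nor is there a validity problem: type I error is not inflated, and the primary analysis and the 174 patients are untouched. It is a cheap improvement, optional rather than required.

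**What to change.** Specify the following before unblinding; Trial status reports that recruitment is complete and the study is still running.

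1. Stratify the Wilcoxon tests (van Elteren weights) and the Jonckheere-Terpstra tests by region. Obtain the trend p value by permutation within strata so that it stays exact.
2. For grip strength, MRC sum score and I-RODS, make the pairwise tests rank analyses of covariance of change on baseline, stratified by region. For INCAT, stratification by region is enough.
3. Keep the planned unadjusted tests, with the Hodges-Lehmann estimate and Moses interval, as supportive, and say in advance which result leads if they disagree.
4. Name the weights and the residualising step. Avoid unweighted strata and adjustment of the final score.

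The cost is some wording and standard programming; baseline and region are already collected. The small downside is that the adjusted rank test has no directly matching interval.
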